### Measures

The primary endpoint is the proportion of invitees who attend screening in each incentive group. This anonymised information will be extracted from the Screening Service database. For those participants who attend their screening appointment, data on their screening outcome score will be collected, aggregated by intervention group.

Demographic information will be collected for all invited participants on age, deprivation score and distance from screening center. Age data will given in deciles, starting from the lowest eligible age of 16 (i.e. 16–25, 26–35 etc.) with those aged 86 years and over being in the highest category. Deprivation scores will be measured based on the Indices of Multiple Deprivation score [35], which is based on postcodes, and will use the address to which the invitation is posted. This data will be given in deciles to ensure participant confidentiality. Distance to screening site will be measured based on the straight-line distance between the address on the day of screening, and the screening site, rounded to the nearest kilometre. Baseline demographics will also be collected for: gender, years registered, and years since last attended screening.

If participants telephone the screening center to opt not to participate in screening, the reason(s) provided will be recorded.

In all groups, when patients arrive, the screener will ask them for any reasons why they have not attended their past few appointments, in order to see if there are differences between intervention groups, and to explore common barriers to attendance in this hard-to-reach group. Reasons given will be noted in a table containing common reasons for non-attendance, along with the intervention group assignment. The reasons suggested are those given by patients in some informal telephone research conducted by 1st Retinal Screen Ltd (shown in Table 1).

**Table 1 Tab1:** Suggested reasons for past non-attendance

Suggested reasons for non-attendance	
Forgot	
Didn't know had an appointment	
Didn't get round to coming	
Was out of the country	
Started experiencing problem with eyes	
Did not feel obviously had problems with eyes	
Couldn't get time off work	
Didn't understand why needed to be screened	
Thought optician did it	
Family commitments	
Too ill to attend	
Seen privately	
Problems with transport	
Do not consider themselves diabetic	
Under the care of Hospital Eye Services	
Other - please specify	

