### Sample size calculation

The primary endpoint is the proportion of the study group who attend their diabetic retinopathy screening appointment. As the study group will comprise patients who have not attended screening for at least two years, including some who have never attended, despite previous interventions to encourage them to attend, this is a very hard to reach population. Attendance in the control group is expected to be extremely low, such as a nominal 1 %. As the eligible study population also tends to be the sickest, with the greatest risk of having retinopathy, and of losing their sight, even a small increase in attendance would have clinical and social benefit.

An increase in attendance of 10 % was deemed clinically significant. A 10 % increase was also considered achievable, as a study found that smoking cessation rates among employees of a large company increased from 5 % to 14.7 % with financial incentives [36], and in another study, warfarin adherence among subjects requiring anticoagulation management improved from 65 % to 97.8 % with a lottery based financial incentive [14]. With two intervention groups, each being compared to the control group, maximum statistical efficiency is achieved by randomising 1.4:1:1. Combining this with an assumed increase in attendance of 10 %, from 1 % in the control arm to 11 % in an intervention arm, there would be 95 % power if 1000 participants were recruited in total (412 in the control group, and 294 in each of the intervention groups). This sample size would also give the study at least 85 % power to detect a smaller increase from 1 % to 7.5 %, which would also be a clinically significant improvement in attendance rates. Should attendance in the control group turn out to be 5 %, the study would still have approximately 85 % power to detect an increase in attendance of 10 % to a level of 15 % in an intervention group [37].

Data from 1st Retinal Screen Ltd suggests that the study group could comprise over 1000 patients. This would allow oversampling at the randomisation stage, so that the intended sample size will still be reached even if participants become ineligible following randomisation (the most common reason for this is most likely to be due to participants attending their routine screening appointments).

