#### Pairwise comparisons

After summary statistics are analyzed, pairwise comparisons of success, or attendance, rates (absolute risk differences) will be performed between the following groups using Chi-square tests adjusting for multiple comparisons:Control vs. Fixed incentiveControl vs. Lottery incentiveFixed vs. Lottery incentive

Risk differences and risk ratios (i.e., relative risks), along with their 95 % confidence intervals, will be presented to assess whether any significant differences between groups exist. This analysis will address the first two research questions of whether financial incentives, and then the design of the incentive scheme have an impact on screening attendance.

Further analyses will be conducted to explore the third research question about whether the incentive schemes attract patients with a different socioeconomic or demographic status. Although groups will be checked after randomisation on the basis of demographic factors, an exploratory subgroup analysis will be performed for adjustment of treatment effect by accounting for the available demographic covariates listed above using a multivariate logistic regression analysis, and performing model selection using a backward stepwise removal process based on a 0.05 significance level; covariate-adjusted differences in success, or attendance, rates between treatment groups will be computed. Significant associations will be identified by those with *p*-values < 0.05, while possible trends toward significance will be identified from 0.05 ≤ *p*-values < 0.10. With anticipated relatively low success rates globally, resulting estimates from these subgroup analyses could be unstable [38, 39], hence affecting possible reliability of the estimates which is why we emphasize the *exploratory* subgroup analysis.

To answer the third research question, comparisons will also be made to those who are classified as regular ‘current’ attenders (i.e., those who have attended at least 2 appointments in the past 3 years) to assess possible differences through demographic covariates and secondary outcome data between regular attenders and non-attenders.

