#### Cost-effectiveness analysis

In order to investigate the fourth research question about the cost-effectiveness of the interventions, a health economics analysis will be conducted. The trial results will provide data on the differential rate of attendance to screening for each group. To assess the short-term cost-effectiveness of the incentives, the cost per additional screening attendee will be calculated as the cost of screening divided by the observed increase in the number of screening attendees for each pairwise comparison of groups.

A longer-term, 5 year, perspective of the cost-effectiveness of the incentives will be assessed using a Markov model. The model will assess the cost-effectiveness from the NHS perspective using the differential rates of screening attendance for each group. The long-term effects of attending screening in terms of the sensitivity of screening, treatment costs and quality of life, as well as the long-term effects of not attending screening, will be determined from the published literature. The costs across the groups will differ only in the monetary incentives provided.

The analysis pertaining to the third research question will indicate if the incentives for attending screening are associated with individual characteristics. If this is the case, the published literature will be consulted to determine if the significant characteristic(s) also impact on the costs and/or quality of life of individuals with diabetes. If so, this will be reflected in the modelling of future costs and quality of life. Sensitivity analysis will be conducted to determine the impact upon cost-effectiveness of changes in the key parameters within the model.

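### Backward removal at p<0.05 conflicts with the plan's 0.05–0.10 trend band for retained covariates and reports only covariates that pass, with inflated estimates that can trigger a change to the economic model

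*Protocol article*

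**What the plan says.** Under Pairwise comparisons, the Protocol article addresses research question 3 with a multivariable logistic regression on the available demographic covariates, "performing model selection using a backward stepwise removal process based on a 0.05 significance level". Covariate-adjusted differences between arms are to be computed. Two labels follow: "Significant associations will be identified by those with" p below 0.05, "while possible trends toward significance will be identified from 0.05" up to 0.10. The text does not say which model or which terms the labels apply to. It calls the analysis exploratory and warns that low attendance may make the estimates unstable.

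The candidate covariates are in Measures: "Demographic information will be collected for all invited participants on age, deprivation score and distance from screening center", and "Baseline demographics will also be collected for: gender, years registered, and years since last attended screening". Age comes in ten-year bands and deprivation in deciles.

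The Cost-effectiveness analysis section uses this analysis as a trigger. If the incentives prove to be associated with individual characteristics, the literature is searched for an effect of the significant ones on costs or quality of life. "If so, this will be reflected in the modelling of future costs and quality of life".

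**The concern.** Two things look wrong. First, one threshold removes what the other is meant to describe: a rule that drops covariates at 0.05 leaves none in the final model with a p-value between 0.05 and 0.10. Second, the reader is shown only the covariates that passed, with p-values and intervals computed as if the final model had been fixed in advance. With few attenders, a weak real association passes only when chance has enlarged it, so it is overstated whenever it is reported.

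At stake is the answer to research question 3 (who the incentives attract). Through the trigger, research question 4 (cost-effectiveness) is also exposed.

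**Working it through.** **Inputs.** From Sample size calculation: "412 in the control group, and 294 in each of the intervention groups", and attendance "from 1 % in the control arm to 11 % in an intervention arm". The same section gives 1% vs 7.5% and 5% vs 15% as alternatives. There are six candidate covariates (Measures). Assumptions not in the document: two-sided Wald tests, arms kept in the model, six independent one-df covariates, and effects expressed per SD.

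**The plan's own figures.** It gives none for the selection step. The arm sizes do reproduce: 1000 × 1.4/3.4 = 411.8 and 1000/3.4 = 294.1. Expected attenders are 412 × 0.01 + 2 × 294 × 0.11 = 4.1 + 64.7 = 68.8.

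**Step 1, the trend band.** A one-df covariate in the final model has p < 0.05 by the removal rule. Simulation of the rule put 0% of final models in the band for such a covariate. The band was reached elsewhere:
- by an adjusted arm contrast in about 5% of runs;
- by some level of an eight-level factor in 54% of the runs that kept the factor (assumed linear trend from −0.6 to 0.6 in log-odds);
- by some covariate in the full model before removal in about 27% of runs with all covariates null.

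**Step 2, false leads.** For six null covariates, 1 − 0.95^6 = 26.5%. Simulated backward removal kept at least one in 28% (1/11/11%), 26% (1/7.5/7.5%) and 25% (5/15/15%) of trials. In a like-for-like run of 1,500 trials, removal gave 26.0% and the full model read at p < 0.05 gave 26.9%. Elimination therefore does not create these false leads.

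**Step 3, size of what is reported.** A hand approximation for a one-SD covariate:
- Information = 412 × 0.01 × 0.99 + 588 × 0.11 × 0.89 = 4.08 + 57.57 = 61.64, so SE = 1/√61.64 = 0.127.
- The smallest odds ratio above 1 that can be retained is exp(1.96 × 0.1274) = exp(0.250) = 1.28.
- For a true odds ratio of 1.20, log-OR = 0.182 and z = 0.182/0.1274 = 1.43. P(retained) = Φ(1.43 − 1.96) + Φ(−1.43 − 1.96) = 0.30.
- Mean log-OR given retention = 0.182 + 0.1274 × [φ(1.96 − 1.43) − φ(1.96 + 1.43)]/0.299 = 0.330, an odds ratio of 1.39.

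Simulation agrees: retained in 30% to 31% of trials with mean odds ratio 1.40, against a full-model mean of 1.21 over all trials. The same hand formula gives a range over the plan's attendance scenarios:

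| Attendance | Expected attenders | SE | Smallest retainable OR | True OR 1.20 retained | Mean OR if retained |
|---|---|---|---|---|---|
| 1% vs 7.5% | 48.2 | 0.149 | 1.34 | 23% | 1.46 |
| 1% vs 11% | 68.8 | 0.127 | 1.28 | 30% | 1.39 |
| 5% vs 15% | 108.8 | 0.103 | 1.22 | 43% | 1.32 |

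Over other true effects (1% vs 11%, simulated), log-ORs of 0.10, 0.20 and 0.30 were retained in 12%, 37% and 62% of trials, at means of 0.31, 0.34 and 0.38. The full model averaged 0.105, 0.206 and 0.300. The overstatement shrinks as the true effect grows.

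**Step 4, the same filter on the full model.** If only full-model terms with p < 0.05 are read, a true odds ratio of 1.20 again appears in 30% of trials at a mean of 1.40. The distortion comes from showing only what passes. It disappears when every term is shown.

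**Step 5, the economic link.** The trigger is statistical significance in this trial. The literature check asks whether the characteristic affects costs or quality of life. It does not ask whether the association with attendance in this trial is real.

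**The case against.** The strongest reply is that little harm is attributable to elimination itself. A reader might infer that it generates the 26% of false leads, or that it exaggerates effects more than a full model would. The figures do not support either: both are the same when a full model is read only at p < 0.05. This part of the reply stands. The case for change therefore rests on reporting every term, not on fewer false positives.

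A reader might also infer that the trend band is empty throughout. The text does not restrict the band to retained covariates, and it follows directly on the mention of adjusted differences between arms. The conflict is confined to whole one-df covariates in the final model. For those terms it is exact.

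A third tempting reading is that a chance covariate passes straight into the Markov model. It does not. Published evidence of an effect on costs or quality of life must come first, no regression coefficient is said to enter the model, and sensitivity analysis of key parameters is planned. What remains is that this gate tests a different question and cannot screen out a chance association.

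Finally, the plan already labels the analysis exploratory and warns of instability, and the chi-square comparisons for research questions 1 and 2 do not use the selected model. Both points are correct. The warning concerns low attendance, however, not selection, and the label does not prevent the result from being used in the economic analysis.

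**Conclusion.** The concern holds in a limited form. The removal threshold and the trend band contradict each other for covariates retained as single terms. Selective reporting also turns an assumed odds ratio of 1.20 per SD into about 1.40 in the roughly 30% of trials that report it. The corresponding means are 1.32 to 1.46 over the plan's other attendance scenarios. The chance of at least one false lead among six null covariates is about 26% with or without selection.

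The figures assume independent one-df covariates with the arms kept in; correlation or categorical coding would change them. The odds ratio of 1.20 is illustrative, not taken from the document. The primary comparisons are not affected. The point is worth correcting because the method is fixed in the text, the remedy is nearly free, and the output can reach the cost-effectiveness model.

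**What to change.** - Replace the backward removal with one pre-specified logistic model containing arm and all six covariates in Measures. Enter age and deprivation as ordered scores: this gives 68.8/8 = 8.6 attenders per non-intercept parameter, against 68.8/22 = 3.1 if both are categorical. Penalised likelihood is optional.
- State how people who have never attended are handled for years since last attended. Sample size calculation says the population includes some, and the variable is undefined for them.
- Report every estimate with its 95% confidence interval, whatever its p-value, and delete the 0.05–0.10 trend category.
- For research question 3, report arm-by-covariate interaction estimates with intervals, labelled exploratory. Main effects alone do not show whether the incentives attract different people.
- Confine any change to the Markov model that rests on these results to a sensitivity analysis.

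The cost is a change of analysis wording, with no new data. Intervals for individual covariates become slightly wider. The interaction intervals will be wide, since only about 4 control attenders are expected (412 × 0.01). The chance of a false p < 0.05 among null covariates stays at about 26%, so individual terms should not be read as findings on their p-values alone.

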#### Cost-effectiveness analysis

In order to investigate the fourth research question about the cost-effectiveness of the interventions, a health economics analysis will be conducted. The trial results will provide data on the differential rate of attendance to screening for each group. To assess the short-term cost-effectiveness of the incentives, the cost per additional screening attendee will be calculated as the cost of screening divided by the observed increase in the number of screening attendees for each pairwise comparison of groups.

A longer-term, 5 year, perspective of the cost-effectiveness of the incentives will be assessed using a Markov model. The model will assess the cost-effectiveness from the NHS perspective using the differential rates of screening attendance for each group. The long-term effects of attending screening in terms of the sensitivity of screening, treatment costs and quality of life, as well as the long-term effects of not attending screening, will be determined from the published literature. The costs across the groups will differ only in the monetary incentives provided.

The analysis pertaining to the third research question will indicate if the incentives for attending screening are associated with individual characteristics. If this is the case, the published literature will be consulted to determine if the significant characteristic(s) also impact on the costs and/or quality of life of individuals with diabetes. If so, this will be reflected in the modelling of future costs and quality of life. Sensitivity analysis will be conducted to determine the impact upon cost-effectiveness of changes in the key parameters within the model.

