### Study design and procedure

The study design will be a three-arm randomized controlled trial. The effect of two different types of financial incentives will be compared to a control group with no incentives. The list of eligible participants identified by 1st Retinal Screen Ltd will be randomized by the statistician (according to an anonymous identifier), prior to the start of the study. No personal information about participants will be shared by 1st Retinal Screen Ltd. For *n* eligible participants provided in the list, they will be indexed according to numbers generated at random with double precision, to avoid duplicates. Participants will then be sorted from smallest to largest according to this random index. Within the sorted list and using the 1.4:1:1 randomisation ratio, we will assign: (1) the lowest n/3.4 participants to the fixed incentive group; (2) the following n/3.4 participants to the probabilistic incentive group; and (3) the remainder of the participants to the control group. We will round n/3.4 to the closest integer, if needed. Participants will be sent a letter by 1st Retinal Screen Ltd inviting them to their appointment, however they will be able to reschedule this appointment once (by phoning a number given on the letter), and still be eligible for the incentive. The letter sent will be determined by the intervention condition to which participants are assigned; these are described below.

The study will take place at a DES clinic based within St Mary’s Hospital, Imperial College Healthcare NHS Trust, in London, UK. Dedicated clinics will be arranged for trial participants, and for each of the intervention groups, so that non-trial patients are not aware of incentives offered to trial patients, and so participants within different groups are not aware of the different incentive conditions. A researcher will be present at the screening sessions for the intervention groups, in order to be able to answer any questions about the incentive, and to give the cash incentive to those in the fixed incentive group. As there will be designated clinics for each intervention group, it will not be possible for the researcher or screener to be blinded to the group assignment. However, as attendance at the clinic is the primary outcome, the study results cannot be biased by the lack of blinding at this stage. The study procedure is shown in Fig. 1.

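### The short-term cost per additional attendee leaves out the incentive payments and, against control, subtracts raw counts from arms of 412 and 294

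*Protocol article*

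**What the plan says.** The Cost-effectiveness analysis section gives the short-term ratio a purpose and a formula. The purpose: "To assess the short-term cost-effectiveness of the incentives, the cost per additional screening attendee will be calculated". The formula: "calculated as the cost of screening divided by the observed increase in the number of screening attendees for each pairwise comparison of groups".

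Three other statements bear on it.
- The sentence just before the formula speaks of rates, not counts: "The trial results will provide data on the differential rate of attendance to screening for each group".
- The paragraph on the 5-year model ends: "The costs across the groups will differ only in the monetary incentives provided".
- The Discussion prices screening 1,000 people at £20,700 and, as a separate item, a £10 incentive for all of them at £10,000.

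Allocation is unequal. Study design and procedure assigns people "using the 1.4:1:1 randomisation ratio", and the Sample size calculation gives 412 in control and 294 in each incentive arm. The Pairwise comparisons section lists control vs fixed, control vs lottery, and fixed vs lottery.

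**The concern.** The fourth research question asks whether offering incentives is cost-effective, and the short-term ratio is the economic measure taken most directly from the trial data. The stated formula has two faults.

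First, the numerator is the cost of screening. The incentive goes to everyone who attends in an incentive arm, including those who would have come anyway, and a ratio meant to judge the incentive does not count it.

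Second, the denominator is an increase in the number of attendees. Control has about 40% more people than either incentive arm, so equal attendance rates do not give equal counts, and a difference in counts is not a treatment effect.

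Followed literally, the formula gives a figure that does not measure what the incentive costs per extra person screened.

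**Working it through.** **Inputs.** Arm sizes 412 and 294, and attendance scenarios 1% vs 11%, 1% vs 7.5% and 5% vs 15% (Sample size calculation). Unit screening cost £20,700 / 1,000 = £20.70 (Discussion). Fixed incentive £10 per attender (Conditions).

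**The plan's own figure.** The article gives no value for the ratio. Its arm sizes reproduce: 1000 / 3.4 = 294.1, rounded to 294; control = 1000 − 2 × 294 = 412.

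**Denominator, incentive arm vs control.** Write pT for attendance in the incentive arm and pC for control. Raw increase = 294·pT − 412·pC. Like-for-like increase = 294·(pT − pC).

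| Scenario | Raw increase | Like for like | Raw is too low by |
|---|---|---|---|
| 1% vs 11% | 32.34 − 4.12 = 28.22 | 29.40 | 4% |
| 1% vs 7.5% | 22.05 − 4.12 = 17.93 | 19.11 | 6% |
| 5% vs 15% | 44.10 − 20.60 = 23.50 | 29.40 | 20% |

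Fixed vs lottery is 294 vs 294 by design, so this fault does not arise there.

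**Numerator: what is left out in the £10 arm.** Incentive per extra attendee = 10·pT / (pT − pC).
- 1% vs 11%: 10 × 0.11 / 0.10 = £11.00
- 1% vs 7.5%: 10 × 0.075 / 0.065 = £11.54
- 5% vs 15%: 10 × 0.15 / 0.10 = £15.00

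**Ratio with both faults corrected.** £20.70 plus the incentive per extra attendee: £31.70, £32.24 and £35.70.

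**Ratio as written.** The article does not say whose screening cost is meant, so two readings were worked.
- *Reading A, screening cost of all incentive-arm attenders over the raw increase:* 20.70 × 32.34 / 28.22 = £23.72; 20.70 × 22.05 / 17.93 = £25.46; 20.70 × 44.10 / 23.50 = £38.85.
- *Reading B, difference in screening cost between the arms over the raw increase:* 20.70 × raw / raw = £20.70 in every scenario and for either incentive. This only returns the unit cost of a screen.

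Under reading A the result is 25% too low at 1% vs 11% (23.72 / 31.70 = 0.75), 21% too low at 1% vs 7.5% (25.46 / 32.24 = 0.79) and 9% too high at 5% vs 15% (38.85 / 35.70 = 1.09).

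**The numerator fault stands alone.** Reading A on a like-for-like denominator, 20.70·pT / (pT − pC), gives £22.77, £23.88 and £31.05, still below £31.70, £32.24 and £35.70.

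**Lottery arm.** The Conditions section ensures that at least one £1000 prize is paid if anyone attends. With about 32 attenders (11% of 294), that is at least 1000 / 32.34 = about £31 per attender, against £10 in the fixed arm. The formula as written registers none of this difference.

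**The case against.** The strongest reply is that the wording is loose and the intention sound. The article condenses a longer protocol. The sentence before the formula speaks of rates, and the pairwise comparisons are absolute risk differences, so the number of attendees might be meant as a scaled number and the cost of screening might be meant to include the incentive. The denominator part of this has some force. The numerator part does not fit the article's own usage, because the Discussion lists screening and incentive as separate costs. Nor is this detail left to another document: the article states a formula, and the formula is wrong as stated.

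Other limits also stand. At the planning rates of 1% vs 11% the count distortion is only 4%, and one of the three pairs escapes it. The two faults pull in opposite directions.

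A reader might infer three stronger things that the document does not support.
- *That the ratio becomes undefined or negative when the incentive works.* With 412 and 294, the raw increase reaches zero at pT = 412/294 × pC, which is 7.0% for 5% control attendance and 1.4% for 1%. The protocol's scenarios all lie well above these values.
- *That the ratio is badly overstated.* Under reading A the net error in the protocol's scenarios runs from 25% too low to 9% too high.
- *That the 5-year model is also wrong, because it says costs differ only in the incentive while more people are screened and treated in one arm.* The same paragraph feeds the model with each group's attendance rate and takes treatment costs from the literature. The natural reading is that cost inputs are common apart from the incentive, while total costs follow attendance.

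**Conclusion.** The concern holds for the short-term ratio only. As written, it omits the one cost that the section says distinguishes the groups. In the £10 arm that is £11.00 to £15.00 per extra attendee, over half of the £20.70 screening cost. In the two comparisons with control, its denominator is too low by 4% to 20% in the protocol's scenarios. The omitted incentive is the more serious fault, since it applies to every pair and at every effect size.

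The figures assume the planned arm sizes, the Discussion's average screening cost applied as a constant unit cost, and £10 paid to every attender in the fixed arm. The net error also depends on which reading of the cost of screening is taken. The primary endpoint, its tests, the sample size and the 5-year model are unaffected.

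**What to change.** Redefine the short-term ratio for each of the three pairs as:

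(mean cost per person invited in one group − the same in the other) / (attendance proportion in the first − the same in the second)

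Cost is the screening cost of those screened plus the incentive or prize payments actually made to attenders, including those who would have come without the offer. Using payments made matters for the lottery arm because of the guaranteed prize.

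In the 5-year model paragraph, at most add that unit costs are common to all groups apart from the incentive and that totals follow each group's attendance.

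This is a change of wording before analysis. It needs attendance, payments made and a unit screening cost, and no new participants or data collection.
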